#### Monitoring of safety data by the DSMB

Safety information will be reported to the DSMB in an unblinded manner. A statistical penalty will not be assessed for the ongoing unblinded review of safety by the committee. Unblinded data will not be released to site investigators unless necessary for safety reasons. If requested by the DSMB, other unblinded data will be reported to investigators. It is necessary for the purpose of monitoring the safety of the study that the committee review not only adverse events (AEs) and SAEs, but also other data that may reflect differences in safety between groups, including retention rates and reasons for dropout.

Expedited review by the medical monitor will occur for all events meeting the FDA definition of SAE. SAEs include any event that a study investigator or the DSMB judges to impose a significant hazard, contraindication, or side effect. The following SAEs will be reported in REDCap within 24 h: deaths, hospitalizations, fatal and non-fatal drug overdose, and psychiatric hospitalizations. For purposes of this study, all SAEs will be required to be reported to the DSMB, regardless of any judgment of their relatedness to the study, at regular meetings. If the medical monitor deems the SAE to be study related, it will be immediately reported (within 24 h) to the DSMB via email, to the IRB if the risk to subjects was previously not known (i.e., consent/protocol change necessary), and to the NIDA Program Official by email. Unfortunately, SAEs such as fatal and non-fatal overdose are expected due to the study population. All relevant information about the event and its outcome, study condition, concomitant medications, the subject’s medical history and current conditions, and laboratory data will be reported. Information will be reviewed and a determination made of whether there was any possible relevance to the study interventions. Reporting to the IRB will be completed according to guidelines. Reporting to the NIH will be made according to their respective regulations governing SAEs. SAE reporting to the DSMB will occur at the regular meetings, unless deemed significant and related to the study.

Adverse events for this study are defined as suicidal intent or plan, injection drug use-associated infection, non-injection drug use-associated infection, new onset liver failure, new onset renal failure, and complications of phlebotomy performed at the SSP. AEs will be collected for this study during the 12-month period after randomization. SAEs are categorized above. AEs will be reported in REDCap within 7 days and presented to the DSMB and IRB yearly.

At yearly intervals during the course of the study and at completion, the IRB and the DSMB will be provided with unblinded summaries of the numbers and rates of AEs by study arm. These reports will include types and severity of events. Data on individual non-serious AEs is not expected to be needed for this review.

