### Composition of the data monitoring committee, its role and reporting structure {21a}

To fulfill its mission of ensuring the safety and integrity of the study, it is necessary that the Data Safety Monitoring Board (DSMB) be comprised of members who possess a high degree of competence and experience, as well as the ability to function independently of all other parties involved in the study. The DSMB members will function free of the career and financial interests of its members and DSMB consists of three members with experience in conducting clinical intervention research on HIV treatment, expertise in biostatistics, and a thorough knowledge of clinical trial ethics and human subject protection issues. The DSMB chair is [name]. [name] is the harm reductionist. The biostatistician is [name]. [name] will serve as medical monitor.

The DSMB will meet annually by zoom conference and be updated semi-annually by report. At the yearly meeting, members will review randomization data as well as adverse events. The following serious adverse events (SAEs) will be reported within 24 h: deaths, hospitalizations, fatal and non-fatal drug overdose, and psychiatric hospitalizations.

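### The protocol gives two conflicting rules for when a study-related serious adverse event reaches the DSMB: within 24 h on relatedness alone, or at the regular meeting unless the event is also 'significant'

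*Protocol article*

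**What the plan says.** The protocol article, under Monitoring of safety data by the DSMB, sets a baseline for every serious event: "all SAEs will be required to be reported to the DSMB, regardless of any judgment of their relatedness to the study, at regular meetings". It then adds a faster route: "If the medical monitor deems the SAE to be study related, it will be immediately reported (within 24 h) to the DSMB via email". That sentence also sends the event to the NIDA Program Official by email and, if the risk was not previously known, to the IRB. The section ends with a third statement: "SAE reporting to the DSMB will occur at the regular meetings, unless deemed significant and related to the study".

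The meeting schedule is under Composition of the data monitoring committee: "The DSMB will meet annually by zoom conference and be updated semi-annually by report". On what is reviewed, the same section says: "At the yearly meeting, members will review randomization data as well as adverse events". Under Other safety-related reports, the semi-annual report covers data quality and completeness, participant flow, visit compliance and key baseline data. SAEs are not among its listed contents.

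**The concern.** The first two statements fit together: every SAE is tabled at a regular meeting, and one judged study related is also sent at once. The closing sentence does not fit. It makes the meeting the only route unless an event is both significant and related, whereas the 24 h rule asks only whether it is related. The added word has no definition in the section and no named decider, while the 24 h rule names the medical monitor.

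Timely notice is at stake. Under Other safety-related reports, the DSMB may recommend termination at any time if risk outweighs benefit, and related serious events are central to that judgement. A site or medical monitor following the closing sentence could hold back a related event that the 24 h rule would send, and could cite the protocol for doing so.

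**Working it through.** The protocol gives no figure for this point, so the check is mainly a comparison of the two rules.

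**Rule A** (24 h sentence). Trigger: SAE deemed study related. Decider: medical monitor. Deadline: 24 h. Channel: email to the DSMB.

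**Rule B** (closing sentence). Default: regular meeting. Exception: significant and related. Decider, deadline and channel for the exception: none given.

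| SAE | Rule A | Rule B | Conflict |
|---|---|---|---|
| Not related | regular meeting | regular meeting | no |
| Related, deemed significant | within 24 h | excepted from meeting-only reporting | no |
| Related, not deemed significant | within 24 h | regular meeting | **yes** |

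**Length of the wait in the third row under Rule B.** Meetings are annual and adverse events are reviewed at the yearly meeting, so the wait is anything up to about 12 months. If the semi-annual report did carry SAEs, which its description does not say, the longest wait would be about 6 months.

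**Enrolment during that wait, as an upper bound.**

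- Inputs: 240 participants (Sample size); recruitment from 10 October 2022 to 30 April 2025 (Trial status).
- Duration: about 30.65 months.
- Steady accrual: 240 / 30.65 = 7.83 per month.
- Over 12 months: 7.83 × 12 = 94, and 94 / 240 = 39% of the sample.
- Over 6 months, if the semi-annual report carried SAEs: 7.83 × 6 = 47.

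The figure of 94 needs a full 12-month wait that lies wholly inside the recruitment period. The event must then fall in the first 30.65 − 12 = 18.65 months. Later events, including those in follow-up after enrolment has closed, have fewer new randomisations behind them, or none.

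**Whether other text settles the third row.** The 24 h list of deaths, hospitalisations and overdoses appears twice. In the safety monitoring section its destination is REDCap; in the DSMB composition section no recipient is given. Neither says that the report goes to the board. Expedited review by the medical monitor covers all events meeting the FDA definition of an SAE, but it is a step before notice to the board and does not replace it.

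**The case against.** The best defence is that the 24 h rule is the operative one. It names the decider, trigger, deadline, channel and recipients, while the closing sentence names none of these and reads like a loose recap. A specific rule would normally prevail, and then nothing is delayed. That is a fair reading and probably the intended one. However, the text does not say which sentence governs, and the recap adds a condition that the rule lacks.

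A second defence is that every SAE is significant by definition, since "SAEs include any event that a study investigator or the DSMB judges to impose a significant hazard, contraindication, or side effect". That sentence says what SAEs include. It does not say that all SAEs are significant, and if they were, the qualifier would do no work.

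A third defence is that other safeguards remain: medical monitor review, REDCap entry, and notice of related SAEs to the NIDA Program Official. This stands, and it confines the gap to DSMB notice.

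A reader might infer more than the text supports:

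- **A third, broader trigger.** The case review includes "a determination made of whether there was any possible relevance to the study interventions". That phrase carries no recipient or deadline, so no sentence expedites an event on possible relevance alone. There are two triggers, with one gap between them.
- **A board unable to classify an event as serious.** The protocol does say "Data on individual non-serious AEs is not expected to be needed for this review". That is an expectation, not a bar. Adverse events are presented to the board yearly, with types and severity by arm, and nothing stops it from asking for more.
- **A filter applied by people who know the arm.** The trial is open-label and the SAE report includes the study condition. But since no one is named to judge significance, the text does not show who would apply the filter.
- **An expected number of participants affected.** The protocol gives no frequency for related SAEs deemed not significant, so neither the average wait nor the average number randomised can be derived.

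**Conclusion.** The contradiction is real and confined to one case: an SAE judged study related but not deemed significant. For that case, notice to the DSMB is due within 24 h under one sentence and may wait up to about 12 months under the other, and no other section settles which applies.

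The 12-month figure assumes that the closing sentence is followed, that regular meetings are the annual ones, and that the semi-annual report carries no SAEs. The figure of about 94 further randomisations (39% of 240) also assumes steady accrual throughout the wait. It is a ceiling. If the 24 h rule governs, neither delay arises. The point concerns the timing of notice to the board, not whether serious events are captured or reviewed. It should be corrected because it bears on safety oversight during enrolment and costs almost nothing to fix.

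**What to change.** Reconcile the two sentences under Monitoring of safety data by the DSMB so that one trigger, one decider and one timeline apply. The simplest edit is to delete 'significant and' from the closing sentence, which then agrees with the 24 h rule already stated, with the medical monitor as decider. If the sponsor and the DSMB do want a significance condition, they should define it, name who judges it, and put the same condition in the 24 h sentence.

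The cost is a short wording change to the protocol, with the DSMB charter checked for the same wording and IRB approval as for any amendment. At most a few additional emails to the board would follow. No data collection, analysis or sample size changes.

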### Adverse event reporting and harms {22}

It is unlikely that participants will be at substantial risk for harm as a result of study participation. They will be prescribed ART and be monitored for potential medication side effects as part of their clinical care outside of specific study labs. Any drug-related toxicities (e.g., elevated creatinine) will be monitored by the study team. Additionally, participants may find some of the questions asked in the questionnaire to be upsetting. Study labs will be conducted routinely and may cause slight discomfort. There is always the potential risk of loss of confidentiality, but procedures are in place to prevent this potential risk. Using telehealth, it is possible that a sign or symptom could be missed. Peers will assist the physician and psychologist in physical diagnosis by taking photos of any wounds and securely emailing them to the clinicians. In-person exams are available at the SSPs. The physician will conduct a thorough review of systems.

We will enroll PWID with HIV initiating ART who will be queried for new potential adverse events at each research visit after screening informed consent. In the THR arm, peer harm reduction counselors will receive training to address medication non-adherence, sexual and injection risk taking, and substance use behaviors. The clinical psychologist will be available on-demand for any participant in either study arm experiencing severe emotional distress, suicidality, or homicidality. He will be backed up by the five study clinicians who have a rotating on-demand call schedule. Additionally, the SSPs have licensed mental health counselors on staff in the case of mental health crisis. During the behavioral assessments, the REDCap survey will automatically indicate provide an alert for a score on the CES-D that suggests that the person is experiencing severe depressive symptoms. Any necessary linkage to emergency services will be provided. With respect to blood draws, each of these procedures will be carried out phlebotomists trained to work with PWID or study physicians to minimize the accidental injury or discomfort to the participants. Participants who experience harm as a result of these procedures will receive first aid from study staff and referral to medical professional if needed.

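### Drug toxicities the study team is said to watch have no place in the adverse-event list, and organ failure and suicidal intent have two possible reporting routes with no rule between them

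*Protocol article*

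**What the plan says.** Three sets of statements bear on this point.

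- **Toxicity.** Adverse event reporting and harms {22} says participants will "be monitored for potential medication side effects as part of their clinical care outside of specific study labs". The next sentence adds: "Any drug-related toxicities (e.g., elevated creatinine) will be monitored by the study team".
- **Adverse events.** Monitoring of safety data by the DSMB opens its definition with "Adverse events for this study are defined as suicidal intent or plan, injection drug use-associated infection", continues with infections not associated with injection, and closes with "new onset liver failure, new onset renal failure, and complications of phlebotomy performed at the SSP". On timing it says: "AEs will be reported in REDCap within 7 days and presented to the DSMB and IRB yearly". The DSMB and IRB receive AE numbers and rates by arm each year, and data on individual non-serious AEs are not expected to be needed for that review.
- **Serious adverse events.** The same section says: "Expedited review by the medical monitor will occur for all events meeting the FDA definition of SAE". It widens the class further: "SAEs include any event that a study investigator or the DSMB judges to impose a significant hazard, contraindication, or side effect". A separate list of events to be entered in REDCap within 24 hours names deaths, hospitalizations, fatal and non-fatal overdoses, and psychiatric hospitalizations.

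On the start of AE enquiry, section {22} has participants "queried for new potential adverse events at each research visit after screening informed consent", while the DSMB section collects AEs for the 12 months that follow randomization.

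**The concern.** The AE definition decides what is counted in the by-arm safety tables. If the plan says a kind of harm is watched but gives it no category, the observations may stay in clinic notes and not reach the body that compares the arms. Both arms can receive antiretrovirals, hepatitis C drugs and medication for opioid use disorder. The trial randomizes how these are delivered, so a difference in tolerability or in how well toxicity is picked up is something the DSMB would want to see. The DSMB section itself says the committee needs data that may reflect between-arm differences in safety.

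The second issue is classification. Where an event is named on one route and may also satisfy the criteria for another, two sites can file the same event differently, and the urgent ones can be filed late.

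**Working it through.** No sample size, error rate or event count enters this point, and the plan gives no figure to reproduce. The check sets the passages side by side.

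**Step 1. Is the AE list closed?** The DSMB section says what AEs are for this study; it does not offer examples. The SAE sentence, by contrast, is worded to include further events. The AE list therefore reads as complete, with six categories: (i) suicidal intent or plan, (ii) infection associated with injecting, (iii) other infection, (iv) liver failure, (v) renal failure, (vi) complications of blood draws at the syringe services program (SSP).

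**Step 2. Where does a raised creatinine go?** This is section {22}'s own example.

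| Possible route | Does it apply? |
|---|---|
| AE categories (i) to (iii), (vi) | No |
| AE category (iv) or (v) | Only if it amounts to new organ failure |
| SAE, FDA definition | Only if serious |
| SAE, judged a significant hazard or side effect | Only if an investigator or the DSMB so judges |
| By-arm AE summary otherwise | No stated path |

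Toxicity that is neither organ failure nor an SAE is thus said to be watched but has no stated way into the summaries.

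**Step 3. Is the watching likely to be even between arms?** Section {22} places side-effect monitoring in clinical care. Under Off-site linkage to HIV care arm, control participants are not linked to study clinicians. The laboratory tests named in Plans for assessment and collection of outcomes {18a} do not include creatinine. Monitoring through clinical care may therefore be better informed in the Tele-Harm Reduction (THR) arm, which is a reason to ask both arms the same question at study visits.

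**Step 4. Which route do the three more severe listed events take?**

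| Event, without hospital admission | Named on the AE list | Named on the 24-hour list | Can meet the general SAE criteria |
|---|---|---|---|
| New liver failure | Yes | No | Yes |
| New renal failure | Yes | No | Yes |
| Suicidal intent or plan | Yes | No | Yes |

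The AE route allows 7 days to REDCap. The SAE route requires expedited review by the medical monitor, and its stated REDCap limit is 24 hours for the named events. If that limit is taken to apply to every SAE, the gap in time to REDCap is 7 days − 1 day = 6 days. The section points back to its SAE text but does not say that an event fitting both descriptions follows the SAE route.

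**Step 5. Start point.** Enquiry from screening consent and collection from randomization cannot both define the AE window. Events before randomization belong to no arm, so this does not alter by-arm rates.

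**The case against.** The strongest reply is that monitoring a toxicity in clinical care and listing it as a reportable AE are different acts, so nothing is contradicted; a short, targeted AE list is a legitimate choice. That stands as far as it goes: this is a gap in capture. But the plan names the toxicity, assigns it to the study team and then leaves it no category, which is worth closing.

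A second reply is that the SAE text already catches what matters. This also stands in part. A toxicity that leads to admission, or is judged a significant side effect, is an SAE and goes to the DSMB whatever its relatedness. A reader might infer that toxicities can never be reported, or that serious organ failure is confined to the slow route. The documents support neither reading. What is absent is a sentence of precedence. Section {22} also provides an on-demand psychologist for suicidality in either arm, so the point concerns reporting and not the immediate response.

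A reader might also set a yearly DSMB presentation for AEs against 24 hours for SAEs. That comparison fails: the 24 hours is to REDCap, and SAEs also reach the DSMB at regular meetings unless the medical monitor finds them study related.

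Finally, a reader might infer that counting blood-draw complications only at the SSP tilts the rates toward THR. The documents do not support that. Study laboratory assessments occur in both arms, the number and place of draws by arm are not given, and THR draws on mobile outreach fall outside the wording too. Moving complications of THR's clinical draws out of the by-arm rates would hide a real consequence of the intervention, so no change is proposed there.

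**Conclusion.** The point holds as two modest defects that can be mended cheaply. First, drug toxicity short of organ failure has no stated path to the by-arm AE summaries unless it qualifies as an SAE. Second, liver failure, renal failure and suicidal intent are named on the AE route, can also meet the SAE criteria, and no rule says which route governs; the supportable difference is 7 days against 24 hours to REDCap. This rests on reading the AE list as closed and on the 24-hour limit extending to SAEs beyond those named. The number of events affected cannot be stated, because the article gives no event rates. The differing AE start points are a minor wording matter.

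**What to change.** Reconcile Adverse event reporting and harms {22} with Monitoring of safety data by the DSMB in three places.

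1. Add a drug-toxicity category to the AE list, ascertained in the same way in both arms at the existing 3-, 6- and 12-month visits and from the medical records that participants already agree to release. Record events regardless of attribution where possible.
2. State that a listed AE that also meets the SAE definition follows the SAE route.
3. Give one AE start point in both sections.

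The cost is protocol wording and one added REDCap category, with no new visit or procedure. There will be a few more AE entries and expedited reports. Attribution of a toxicity to a drug may be better informed in the THR arm, where study clinicians deliver care; recording without requiring attribution limits that imbalance but may not remove it.

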If participants have co-occurring mental health disorders, peers can use telehealth to connect the participants to the SSP’s on-site psychologist for mental health treatment. The psychologist will consult with the study clinician about any mental health diagnoses so that appropriate prescriptions can be initiated (e.g., SSRI for depression or anxiety). *THR* medical services include management of HIV, SUD, and other comorbidities. Infections such as skin and soft tissue infections will be treated with antibiotics, and any required procedural intervention will be referred to on-site wound care at the SSP. Physician visits are available to patients on-demand during most business hours and coordinated by the study team. All participants with OUD are repeatedly offered initiation of buprenorphine-naloxone or naltrexone, navigation to methadone programs, and naloxone for overdose prevention. Participants with chronic HCV infection are offered treatment with DAAs. Participants are screened for sexually transmitted infections and navigated to treatment when necessary. THR medical care will take an adaptive approach based on patient vulnerability (e.g., unstable housing, severe SUD, concurrent SUDs) as outlined in the THR Intervention Manual. The adaptive approach will, at the discretion of the study clinician, appropriately address patient needs (e.g., medications for stimulant use, medications for alcohol use disorder). If residential treatment for SUD is requested and appropriate, the peer will work with the participant and SSP staff to link to Ryan White or other treatment beds. This multidisciplinary team will assist the patient for 12 months, bringing the technology (i.e., traveling with iPad and WiFi hotspot) and *THR* to the participant where they are located. After the study period, the study participant will be offered continuation in the *THR* program.

Participants in the *THR* arm will have all intervention sessions audio recorded (i.e., physician, psychologist and peer encounters). Participants will be given the option to opt out of being audio-recorded.

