#### Off-site linkage to HIV care arm

If randomized to off-site linkage to HIV care (control condition), the study staff will introduce the participant to an SSP HIV/HCV linkage specialist and discuss linkage to a traditional Ryan White clinic, Federally Qualified Health Center, or private physician office that treats HIV and HCV (based on the preferences of the study participant). The linkage specialist will activate the Test and Treat process within 7 days and follow standard of care procedures for linking to Ryan White case management and first provider appointment. DAA and MOUD would be received via the off-site clinic. This approach is outlined in the Intervention Manual and will include a warm handoff (i.e., linkage specialist will accompany participant and provide logistical support) to both case management and the clinician. Participants will not be linked to study clinicians but may be linked to other providers within a clinic where study clinicians see patients. At the end of the 12-month study period, patients randomized to off-site linkage arm will be offered entry into the *THR* program.

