## Data collection and management

### Plans for assessment and collection of outcomes {18a}

Data collection is planned at screening, baseline, and at 3-, 6- and 12-month follow-up assessments. Quantitative behavioral questionnaires will be available in English and completed in REDCap under multi-factor authentication at UM. Measures will be included from NIDA’s Data Harmonization projects, particularly NIDA’s Seek Test Treat and Retain for Vulnerable Populations data consortium. Table 1 describes the battery of quantitative assessments planned.

Laboratory assessments will include indicated laboratories in PWID. At screening, these will include HIV RNA to determine eligibility as well as T cell subsets, HCV RNA, HBsAg, HBsAb, anti-HAV, RPR, and 3-site gonorrhea and chlamydia screening. Additional laboratory assessments occur at 0, 3, 6, and 12 months. HIV RNA is measured to confirm primary outcome at 3, 6, and 12 months. HCV RNA and UDS are measured to confirm secondary outcome measures in both arms.

For the cost and cost-effectiveness analyses, we will perform an economic evaluation of *THR* versus off-site linkage to HIV care. We will look at the cost to achieve a unit of effectiveness as defined by the main study and, to the extent possible, will look at this from different perspectives (healthcare, societal). For cost data, we will create custom resource trackers based on the DATCAP method [40]. DATCAP was designed as a program-level costing instrument for standard modalities of SUD treatment.

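### By-arm AE rates could be inflated in the THR arm, because ascertainment between research visits is not equal and the article states no common-route rate

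*Protocol article*

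**What the plan says.** Under Monitoring of safety data by the DSMB, "the IRB and the DSMB will be provided with unblinded summaries of the numbers and rates of AEs by study arm". This happens yearly and at the end of the study, with types and severity shown. The same section says that data on individual non-serious AEs should not be needed for this review.

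On collection, Adverse event reporting and harms {22} has enrolled participants "queried for new potential adverse events at each research visit after screening informed consent", without distinction by arm. The schedule is in Plans for assessment and collection of outcomes {18a}: "Data collection is planned at screening, baseline, and at 3-, 6- and 12-month follow-up assessments". On the time window, "AEs will be collected for this study during the 12-month period after randomization". On entry, "AEs will be reported in REDCap within 7 days"; listed SAEs are entered within 24 h.

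The AE list is closed: suicidal intent or plan, infections (injection-related or not), new liver failure, new renal failure, and "complications of phlebotomy performed at the SSP".

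The arms differ in clinical contact. In the THR arm, "Physician visits are available to patients on-demand during most business hours and coordinated by the study team". Its clinicians treat skin and soft tissue infections, its peers meet participants at medication distributions, and the team stays involved for 12 months. In the control arm, "Participants will not be linked to study clinicians but may be linked to other providers within a clinic where study clinicians see patients".

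**The concern.** A rate is comparable between arms only if an event has the same chance of being recorded in each. Here the common route is a query at three follow-up visits, with a gap of 6 months between the last two. Between visits, a THR participant with an infection may be treated by a study physician. A control participant with the same infection may be treated at an outside clinic, and the study learns of it only if it is recalled at the next visit or comes up at the SSP.

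If events learned through THR encounters enter the AE data, the THR rate would be raised by closer observation alone, or a true excess in control could be masked. The DSMB weighs risk against benefit and may recommend termination (Other safety-related reports), so it should be able to tell observation from harm. The source of an event cannot be recovered later if it was not captured at entry.

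**Working it through.** The article gives no AE rate, detection rate or safety threshold, so there is no figure to reproduce. The first step is to set the routes to knowledge of an AE side by side.

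| Route | THR | Control |
|---|---|---|
| Query at research visits ({22}, {18a}) | yes | yes |
| Study physicians, on demand, treating infections ({11a}) | yes | no |
| Peers at medication distributions ({11a}) | yes | no |
| Routine SSP contact, typically weekly ({18b}) | yes | yes |
| Psychologist for severe distress or suicidality ({22}) | yes | yes |
| Signed medical record release ({26b}); no AE use stated | yes | yes |

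Two routes belong to THR alone, and both can reveal listed AEs. The shared routes other than the visit query are not described as including an AE inquiry.

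The phlebotomy item is tied to place. THR clinical blood draws can happen at the SSP and would count; a control participant's draw at an outside clinic cannot. The item also leaves out THR draws on mobile outreach. Scheduled study labs at 0, 3, 6 and 12 months apply to both arms, so study draws are the common basis.

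The second step is an illustration of size. **All inputs except the arm size are assumptions.** The arm size is 240/2 = 120 (Sample size {14}). Take the same true risk of 30% of having an AE in both arms, full 12-month follow-up, and 90% detection in THR.

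- Expected participants with a recorded AE = 120 × true risk × detection.
- THR: 120 × 0.30 × 0.90 = 32.4.
- Apparent ratio = THR detection / control detection, whatever the true risk.

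| Control detection | Control count | Apparent ratio | Chance of a nominally significant THR excess |
|---|---|---|---|
| 90% | 32.4 | 1.00 | 2.5% |
| 80% | 28.8 | 1.125 | 8% |
| 70% | 25.2 | 1.29 | 19% |
| 60% | 21.6 | 1.50 | 39% |
| 50% | 18.0 | 1.80 | 63% |

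The last column uses Φ((d − 1.96·SE0)/SE1), with SE0 pooled and SE1 unpooled. For 60%:

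- d = 0.27 − 0.18 = 0.09
- SE0 = √(2 × 0.225 × 0.775/120) = 0.0539
- SE1 = √((0.27 × 0.73 + 0.18 × 0.82)/120) = 0.0536
- Φ((0.09 − 0.1056)/0.0536) = Φ(−0.29) = 0.39

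Over true risks of 20% to 50% and control detection of 80% to 50%, the chance runs from 6% to 91%. No such test is planned, so the column is only a yardstick for how visible an artefact would be. The first row is the case in which only the common visit query feeds the table: no bias arises by this route.

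**The case against.** A reader might infer that controls are asked about AEs only at research visits while THR participants are watched continuously, so that equal harm would certainly show as excess harm in THR and could halt the trial. The article does not support that reading.

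- **Contact with controls.** The visit query applies to everyone. Controls also have typically weekly SSP contact and on-demand psychologist access. Wound care is described as an SSP service in general, and in-person exams are available at the SSPs; neither is limited to THR. Infections and suicidal intent could therefore surface in both arms.
- **Mechanism.** Nowhere does the article say that events learned in THR encounters enter the AE table. Reporting deadlines that are not tied to visits suggest entry whenever staff learn of an event, but this is inference.
- **Consequence.** The summaries are descriptive. The DSMB is unblinded, sees types and severity, and applies judgement; no AE test or boundary is stated. Deaths and hospitalizations are probably less affected than the non-serious list.
- **Level of detail.** A source field may exist in the full protocol or case report forms, which are not shown, and its absence from an article is not a fault.

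All of this stands, and it limits the point. It does not remove it. The shared SSP and psychologist contacts come on top of THR's physician and peer contacts and do not offset them. The site monitoring in {23} checks recorded AEs and is not described as finding unrecorded ones. The article itself fixes a by-arm rate and a phlebotomy item tied to place, so the comparison as stated is open to unequal ascertainment.

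**Conclusion.** The point holds as a possible bias, not a demonstrated one. Following the article as written, the by-arm rates of non-serious AEs could be inflated in THR. The amount depends wholly on the gap in detection between arms, which the article does not give; it is zero if only research-visit events are counted. The ratios of 1.125 to 1.80 above rest on assumed detection rates and should not be read as estimates. There is no contradiction in the text, and the primary outcome is not touched. This is a cheap improvement to the safety reporting.

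**What to change.** 1. For each AE and SAE, record how it was found: research-visit query, intervention contact, or other.
2. In the DSMB, IRB and final reports, show the by-arm rate from the common research-visit query beside the all-source rate, and list separately the events known only through THR contacts.
3. Define the phlebotomy item as complications of study blood draws in both arms, wherever they are drawn.

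Do not add abstraction of infection records to the comparable rate, although all participants sign a release. THR encounters are themselves charted in the health record, so abstraction would bring the same imbalance back.

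The cost is one REDCap field and one extra split in the safety tables. The common-route rate will contain fewer events than the total, which is why both should be shown. If the full protocol or case report forms already capture the source, only the reporting split and the phlebotomy wording remain to be done.
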